## Abstract

**Background:**

The objectives of this paper are to describe the planned implementation and evaluation of the Building on Existing Tools to Improve Chronic Disease Prevention and Screening in Primary Care (BETTER 2) program which originated from the BETTER trial. The pragmatic trial, informed by the Chronic Care Model, demonstrated the effectiveness of an approach to Chronic Disease Prevention and Screening (CDPS) involving the use of a new role, the prevention practitioner. The desired goals of the program are improved clinical outcomes, reduction in the burden of chronic disease, and improved sustainability of the health-care system through improved CDPS in primary care.

**Methods/design:**

The BETTER 2 program aims to expand the implementation of the intervention used in the original BETTER trial into communities across Canada (Alberta, Ontario, Newfoundland and Labrador, the Northwest Territories and Nova Scotia). This proactive approach provides at-risk patients with an intervention from the prevention practitioner, a health-care professional. Using the BETTER toolkit, the prevention practitioner determines which CDPS actions the patient is eligible to receive, and through shared decision-making and motivational interviewing, develops a unique and individualized ‘prevention prescription’ with the patient. This intervention is 1) personalized; 2) addressing multiple conditions; 3) integrated through linkages to local, regional, or national resources; and 4) longitudinal by assessing patients over time. The BETTER 2 program brings together primary care providers, policy/decision makers and researchers to work towards improving CDPS in primary care. The target patient population is adults aged 40–65. The reach, effectiveness, adoption, implementation, maintain (RE-AIM) framework will inform the evaluation of the program through qualitative and quantitative methods. A composite index will be used to quantitatively assess the effectiveness of the prevention practitioner intervention. The CDPS actions comprising the composite index include the following: process measures, referral/treatment measures, and target/change outcome measures related to cardiovascular disease, diabetes, cancer and associated lifestyle factors.

**Discussion:**

The BETTER 2 program is a collaborative approach grounded in practice and built from existing work (i.e., *integration not creation*). The program evaluation is designed to provide an understanding of issues impacting the implementation of an effective approach for CDPS within primary care that may be adapted to become sustainable in the non-research setting.

## Background

### Introduction

The purpose of this paper is to describe the planned implementation and evaluation of the Building on Existing Tools to Improve Chronic Disease Prevention and Screening in Primary Care (BETTER 2) program. We will describe the unique approach the BETTER 2 program takes to address chronic disease prevention and screening (CDPS) in primary care settings including the frameworks and evaluation metrics that will be used to measure the effectiveness of the program in achieving its goals.

The paper is divided into the following three broad sections: 1) the ‘Background’ section provides an overview of CDPS in primary care and discusses the BETTER approach to CDPS and the integral role that the prevention practitioner plays in promoting CDPS. This section further reviews the effectiveness of the Building on Existing Tools to Improve Chronic Disease Prevention and Screening in Family Practice (BETTER) trial and describes the evolution of the BETTER 2 program including the specific objectives it seeks to accomplish. 2) The ‘Methods/Design’ section explains the prevention practitioner role and how the BETTER 2 program will expand and adapt to novel jurisdictions. This section further includes a description of the planned evaluation of the BETTER 2 program, which involves qualitative, quantitative, and health economic components. 3) Lastly, the ‘Discussion’ section highlights the unique approach utilized for knowledge integration and the potential outcomes of the proposed program evaluation.

### Background

The prevalence of chronic disease is steadily increasing [1,2]. These chronic diseases have a substantial impact on health-care services and many can be prevented. Primary care is the ideal setting for most CDPS activities. Regrettably, evidence-based tools and strategies for CDPS are inconsistently applied in primary care practice. Barriers to implementing evidence into practice occurs at multiple levels [3] and are, in part, due to competing demands on primary care physicians leaving little time to address CDPS [4,5].

The BETTER trial, a pragmatic randomized controlled trial, previously demonstrated the effectiveness of an approach to CDPS that involved 1) a clinical working group (CWG) which identified and harmonized the evidence for CDPS actions in patients aged 40–65 [6], and 2) an intervention consisting of practice facilitation at the individual patient-level through the use of a prevention practitioner (Figure 1) who was internal to the practice [5,7].

**Figure 1 Fig1:**
[figure not shown]
**The BETTER chronic disease prevention and screening prevention practitioner intervention.**

The prevention practitioner was a new role introduced to the primary care practice setting [7]. In the BETTER trial, the prevention practitioners were health-care professionals (licensed practical nurse, nurse, dietician, nurse practitioner) who worked with the primary care providers to develop a comprehensive approach to evidence-based CDPS within the practice setting [5–7]. Clinicians, researchers, and prevention practitioners with support from the Center for Effective Practice in Toronto, Canada participated on the BETTER CWG which identified the evidence-based clinical guidelines and interventions that were then adapted and incorporated into the BETTER CDPS tool kit [6]. The tool kit included patient surveys, prevention visit templates, prevention prescriptions, a CDPS care map, and patient resources. The prevention practitioner utilized the BETTER CDPS tool kit to evaluate patients and, through a process of shared decision-making, provided the patient with an individualized prevention prescription and CDPS goals.

The original BETTER trial demonstrated that a prevention practitioner ‘can improve the implementation of clinically important prevention and screening for chronic diseases in a cost-effective manner’ [5] in urban multidisciplinary primary care settings in Alberta and Ontario, Canada. Further funding was obtained to disseminate, implement, and evaluate the BETTER 2 program in heterogeneous populations as well as in rural and remote settings.

### Aims of the BETTER 2 program

The overarching aims of the BETTER 2 program are to improve clinical outcomes, reduce the burden of chronic disease, and improve the sustainability of the health-care system through improved CDPS in primary care. The program targets those chronic diseases that have strong evidence for prevention and screening, specifically cancer, cardiovascular disease, diabetes, and their associated lifestyle risk factors in patients aged 40–65.

Specific objectives of the BETTER 2 program are the following:To introduce the BETTER approach to new jurisdictions and deepen the impact in the two original participating provincesTo adapt, revise, and tailor the BETTER individual patient-level CDPS intervention including the survey, tools, actions, and resources for uptake in a variety of settings including remote, rural, aboriginal populations, and disadvantaged populationsTo synthesize BETTER knowledge products for translation, dissemination and exchange through the development of a web resource with updated CDPS tools, actions, and training resourcesTo evaluate the adapted BETTER intervention using a mixed methods approach

## Methods/design

### Intervention (the program)

Experts in research, practice, and policy worked together to develop the BETTER 2 program with the aim of addressing CDPS from a policy and practice perspective including the needs of the end users, such as health-care professionals, a key to integrated knowledge translation [8–11]. Since implementing a new approach and associated changes are often perceived as challenging [12], a comprehensive, multilevel approach that engages both policy makers and practitioners is needed to implement change successfully [3,13]. The Chronic Care Model is an integrated approach with multiple and multilevel strategies that has been demonstrated to be most effective in addressing chronic disease prevention and management [14–16]. This model was also adopted and described by Ontario’s Chronic Disease Prevention and Management Framework [17]. The Chronic Care Model is the foundational framework that informs the BETTER 2 program (see Figures 2 and 3). The BETTER 2 program addresses the knowledge to action gap through obtaining an understanding of the context-specific practical wisdom of the primary care providers in diverse settings and facilitates macrolevel knowledge partnerships between researchers, practitioners, and policymakers [18].

**Figure 2 Fig2:**
[figure not shown]
**Logic model for the BETTER 2 program.**

**Figure 3 Fig3:**
[figure not shown]
**The BETTER 2 mapped onto the chronic disease framework.**

We propose to introduce an intervention that is proactive at both the population and an individual patient-level. The patient intervention consists of a dedicated prevention visit with the prevention practitioner (see Figure 1). The prevention practitioners are health professionals identified by primary care providers and trained by the BETTER 2 program to identify at-risk patients and invite them to a prevention visit. The prevention practitioners further identify local CDPS resources that are reviewed by the CWG to ensure that they are evidence based before being integrated into their BETTER 2 CDPS tool kits.

The program will collaborate with practice, policy, and research partners to expand the prevention practitioner role in Canadian provinces and territories: the Northwest Territories, Newfoundland and Labrador, and Nova Scotia, and deepen the impact in the two original participating provinces, Alberta and Ontario, through providing a framework, tools and resources for CDPS in primary care settings. To accomplish this, the BETTER 2 program, working with partners from each context, will review, revise, and adapt the original BETTER intervention, including the survey, tools, actions, and resources to each setting including urban, rural, remote settings, aboriginal populations, and disadvantaged populations. This will include identifying and cataloging CDPS resources and incentives available to the various communities engaged in the BETTER 2 program and reviewing the BETTER CDPS survey and tools to tailor them to the needs and requirements of those communities.

Presently primary care is focused on acute and chronic disease management and there is often no specific individual and too little time committed to CDPS [7]. The BETTER 2 team will support the prevention practitioners in their new role and work with them to conduct an asset mapping activity aimed to identify local, regional and national resources that the prevention practitioners can integrate into their setting and role. The BETTER 2 CWG will synthesize evidence-based CDPS knowledge products for translation, dissemination and exchange and provide a web resource [19] with updated CDPS tools and actions including training resources such as manuals, webinars and podcasts [20]. The team will also oversee and facilitate the training of the prevention practitioners to develop skills in CDPS including developing an individualized patient prescription.

### Target population

The target populations include (see Figure 2) [17] the following:Activated communities and prepared, proactive community partners including primary care groups and organizations who will help to facilitate the BETTER 2 approach to CDPS through dedicating resources (such as a health-care professional’s time to take on the role of the prevention practitioner). Activated communities and partners will be the ones to support policies and organizational structures and engage in the BETTER 2 program.Informed, activated individuals and families through patient participation. The sites will select and identify at-risk populations such as adult patients of the participating primary care providers who are between the ages of 40 and 65, and data will be obtained from those who provide written informed consent to participate. We chose this age group because this is the age group for which most of the CDPS actions can be applied [5].Prepared proactive practice teams including primary care providers, researchers, and policy/decision makers who will work together with the BETTER 2 team to develop a comprehensive source of tools aimed to transform practice through a patient-level intervention by a health-care professional within the practice, the prevention practitioner.

### Program evaluation using the RE-AIM framework

The BETTER 2 program has developed a logic model that describes the inputs and the anticipated short-term, intermediate, and long-term outcomes (see Figure 2). The program will undergo an evaluation using the RE-AIM (reach, effectiveness, adoption, implementation, maintain) framework [21–23]. Most evaluations of health promotion impact have restricted their focus to one or two of the five dimensions of quality that are believed to be important [22]. RE-AIM provides a comprehensive framework to assess programs that work in the real-world setting [21,22].

#### Reach

The reach of the program will be captured through descriptive information. This will include information on the proportion of the patients approached, who participated, and who returned for follow-up visits including the representativeness of those participating, where possible. In the original BETTER trial, there was a 63% acceptance rate with a return rate of 81.6% at 7 months and 10% (46/444) did not attend any visits [5]. In our rural and more disadvantaged populations, we anticipate that the proportion of patients accepting and following-up on the intervention will decrease and the proportion of patients who do not show up for any visits will increase.

The reach of the program will include the following:The number of patients approached to participate in the program (denominator)The number of patients who agree to participate and who follow-through to actually have a visit with the prevention practitionerThe number of primary care providers/sites approached and educated about BETTER and the proportion that have adopted the tools or adapted the prevention practitioner role into their practicesDemographic information (if available) of participating patients including ethnicity, gender, age, socioeconomic status, and primary care site

#### Effectiveness

The effectiveness of the program will be evaluated using the explicitly defined summary statistics defined below as well as via the use of a more comprehensive composite index [5].

Specifically, effectiveness measures will include the following:The proportion of individual CDPS activities achieved at any point in time. We will identify specific CDPS action information that we can capture in the population at six-month intervals (e.g., proportion of eligible mammograms, blood pressures, alcohol history, smoking status, etc., achieved at 0, 6, and 12 months). We will track the proportion of patients completing these maneuvers longitudinally at each of these observation points.An evaluation of the CDPS achieved using a composite index [24] developed for CDPS and adapted from the original BETTER trial [5]. The composite index is identical in its mathematical definition to the one used in the original BETTER trial; however, the items comprising the composite are different. Informed by the learning experiences in the BETTER trial, we revised the content to get better quality data.

The composite index is comprised of process outcome measures (i.e., monitoring and screening actions), referral and treatment measures (i.e., appropriate treatment of out-of-date or off-target actions), and target/change outcomes (i.e., quantifiable change or improvement actions). The CDPS actions in each patient eligible to complete as part of the program are determined at baseline, and the achievement of these eligible actions is assessed at follow-up. Where possible, a composite index for each patient will be calculated at baseline and then at six-month intervals. If a patient is ineligible (up to date) for all CDPS maneuvers, then his/her contribution to the aggregate composite index is non-calculable as the denominator (the number of eligible items at baseline) is zero.

The composite index will allow for measures of change over time, that is, a gross indicator of effectiveness. The composite index essentially provides an average measure of effectiveness over all people enrolled in the study, and suggests the proportion of conditionally eligible maneuvers (as defined at baseline) which are achieved at follow-up. It acts to average over the heterogeneity of the patients and the maneuvers they are specifically eligible for; hence, it is referred to as a gross measure of effectiveness. For any given patient, the composite index can also act as a benchmark of how the patient is doing with respect to CDPS at any given moment in time. We will use the composite index as a comprehensive measure of CDPS to describe the proportion of eligible actions achieved at six-month intervals, and it will also allow researchers the opportunity to investigate certain comparisons of CDPS effectiveness between group factors, such as jurisdiction, age, sex, etc.

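### Target/change items appear to be scored only in patients eligible at baseline, with no comparator described, so some achievement will be regression to the mean, of unknown size

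*Protocol article*

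**What the plan says.** All of this is in the protocol article, under Methods/design, Program evaluation using the RE-AIM framework, Effectiveness, unless another section is named.

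- The index has three kinds of item: process measures, "referral and treatment measures (i.e., appropriate treatment of out-of-date or off-target actions"), and "target/change outcomes (i.e., quantifiable change or improvement actions").
- One rule covers all three kinds. The actions for which a patient is eligible "are determined at baseline, and the achievement of these eligible actions is assessed at follow-up".
- The denominator is the count of items eligible at baseline. "If a patient is ineligible (up to date) for all CDPS maneuvers, then his/her contribution to the aggregate composite index is non-calculable", because "the denominator (the number of eligible items at baseline) is zero".
- The result is read as effectiveness: "The composite index will allow for measures of change over time, that is, a gross indicator of effectiveness". The same section plans comparisons of effectiveness by jurisdiction, age and sex.
- The mathematical definition is carried over unchanged from the original BETTER trial, which the Background describes as a randomised controlled trial. The Trial status section says that BETTER 2 is a programme evaluation and not a research trial. The article describes no concurrent comparison group.

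The article does not list the target/change items, their cut-offs, the change that counts as success, the number of readings behind eligibility, or the weight of these items in the index.

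**The concern.** If an item rests on a measured value that varies from one reading to the next, the baseline reading does two jobs. It decides whether the patient is in the denominator, and it is the value against which improvement is judged. Patients who were past the cut-off partly by chance will tend to be on the other side next time, with no true change. Patients who were on target by chance and later read off target have no eligible item, so the opposite movement is never counted.

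In a randomised comparison the control arm regresses in the same way, and the difference between arms largely removes the effect. Used without a comparator, the same index keeps it. The target/change part could therefore show apparent improvement under a wholly ineffective programme. These are the items closest to the stated aim of improved clinical outcomes. Comparisons between jurisdictions, age groups or sexes are exposed too, because the spurious rate depends on how common an off-target value is in each group.

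**Working it through.** The article gives no variance, correlation, cut-off or rate for this point, so there is no figure of the plan's own to reproduce. What follows shows the direction, and then the range under assumptions.

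**Model.** Let X1 (baseline) and X2 (follow-up) be standardised readings with correlation r and no true change. A patient is eligible if X1 ≥ c, where q = P(X1 ≥ c) is the off-target prevalence. The values of q, r and the required change d are assumptions.

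**1. Success means crossing back below the cut-off.** The spurious achievement rate is p = P(X2 < c | X1 ≥ c) = 1 − P(X1 ≥ c, X2 ≥ c)/q, from the bivariate normal distribution. It is above zero whenever r < 1.

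| q | r=0.6 | r=0.7 | r=0.8 | r=0.9 | r=0.95 | r=0.98 |
|---|---|---|---|---|---|---|
| 10% | 61% | 53% | 44% | 31% | 22% | 14% |
| 20% | 50% | 44% | 36% | 25% | 18% | 11% |
| 30% | 42% | 37% | 30% | 21% | 15% | 9% |
| 50% | 30% | 25% | 21% | 14% | 10% | 6% |

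The range is about 6% to 61%.

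**2. Why the opposite movement matters.** Take 1,000 patients with q = 20% and r = 0.8, so p = 0.355. There are 200 off target at baseline, and 200 × 0.355 = 71 of them read on target at follow-up. By symmetry 71 of the 800 on target read off target. The share off target stays at 200/1,000, a net change of 0. The index rule sees only 71/200, about 36% achieved.

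**3. Success means an improvement of at least d.** This is P(X1 − X2 ≥ d | X1 ≥ c), simulated with 2,000,000 draws. At q = 20%:

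| d | r=0.6 | r=0.8 | r=0.9 | r=0.98 |
|---|---|---|---|---|
| 0.5 SD | 53% | 36% | 21% | 1% |
| 1 SD | 30% | 12% | 2.5% | about 0% |

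Over q = 10% to 50% and r = 0.6 to 0.98, the 1 SD rule gives about 0% to 36%.

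**4. Illustration on a familiar scale.** Assume systolic pressure, cut-off 140, between-person SD 14 and single readings with within-person SD w. Then r = 14²/(14² + w²), which is 196/245 = 0.80 for w = 7, 196/296 = 0.66 for w = 10 and 196/340 = 0.58 for w = 12. With a population mean of 130, p is 32%, 40% and 44%. Over means of 125 to 135 the range is 26% to 51%. This is the more variable end of the table. The article names blood pressure only among its examples of completed actions, not as a target/change item.

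**5. Effect on the whole index.** If target/change items are a share s of the eligible items, the spurious contribution is s × p. For s from 10% to 40% and p from 10% to 50% this is 0.10 × 0.10 = 1 point to 0.40 × 0.50 = 20 percentage points. Both s and p are assumed.

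**6. Is net change free of the problem?** Only if enrolment does not depend on the baseline reading. Suppose on-target patients are enrolled at half the rate of off-target ones. The spurious net fall in the off-target share is then 0.5qp/[q + 0.5(1 − q)]. In the systolic illustration with mean 130:

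- w = 7: q = 0.261 and qp = 0.083, so 0.0415/0.631 = 6.6 points.
- w = 12: q = 0.294 and qp = 0.130, so 0.065/0.647 = 10.0 points.

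**The case against.** Much can be said for the plan, and most of it limits the size of the point without removing it.

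- **The off-target restriction is inferred.** A reader might take it as the article's own rule that target/change items are scored only in off-target patients. It is not stated. The term off-target is used for referral and treatment items, and ineligibility is glossed as being up to date. The inference is fair, since the eligibility rule is stated for all items alike, but it remains an inference.
- **A large share is not shown.** A reader might conclude that much of the target/change achievement will be spurious. That holds for variable, single-reading items (r about 0.6 to 0.8, crossing a cut-off: 21% to 61%). It does not hold for stable measures or for items that need a sizeable change. Item definitions and any repeat reading may stand in a fuller document, and their absence from a condensed article is no fault.
- **At-risk enrolment is not shown to add to the bias.** The Target population section says "The sites will select and identify at-risk populations such as adult patients" and then gives an age range. Selection on age causes no regression to the mean. If at-risk means a higher population mean, the off-to-on rate in the illustration falls, from 38%, 47% and 51% at mean 125 to 26%, 33% and 37% at mean 135.
- **Only one of three item types is touched.** The examples that the article gives, such as "proportion of eligible mammograms, blood pressures, alcohol history, smoking status, etc., achieved at 0, 6, and 12 months", are mainly about completion.
- **The claim is modest.** The index is called gross, it is meant partly to describe, and the main evidence of effectiveness is placed in the earlier trial. But the article ties gross to averaging over different patients and maneuvers, not to the lack of a comparator, and it still calls the index a measure of effectiveness.

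**Conclusion.** The point holds in a limited form. The rule as stated conditions on baseline status, scores one direction of movement and reads the result as effectiveness with no comparator described. For a target/change item based on a variable measured value, that biases apparent achievement upwards. This follows from a rule that the article fixes, not from missing detail.

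The size is not determinable from the article. It depends on the test-retest correlation, the off-target prevalence and the change required, and the ranges above rest on assumed values and a no-change bivariate normal model. The effect on the whole index depends further on the unstated weight of these items. Process and referral items are outside this mechanism.

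**What to change.** 1. Report the target/change component separately from the process and referral items.
2. For each measured target item, also show the share on target at baseline, 6 and 12 months in all patients to whom the item applies who have both readings, including those on target at baseline. Give the off-to-on moves, the on-to-off moves and the net change.
3. Describe both the conditional index component and the net change as uncontrolled change over time, not as programme effectiveness.

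The cost is one table per measured item where values are already recorded for all patients at the six-month assessments. Apparent improvement will be smaller. Precision will be low where few on-target patients have follow-up readings. Net change is no cure for the missing comparator: it remains a before-after difference, and it is itself biased if sites enrol on the basis of high baseline readings (6.6 to 10.0 points in the assumed example).
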